### Design and Procedures

PD participants will be recruited through the local hospital’s exercise intervention group. To reduce potential expectation bias and confirm eligibility, a research assistant will make telephone contact with those referred by a neurologist and follow up with interested participants. Healthy controls (HC) will be recruited from the local communities through posters during the same recruitment period. Participants with PD will be randomly assigned to one of two groups: Wuqinxi or balance. The total intervention period will be 24 weeks. Primary and secondary outcomes will be assessed at baseline (prior to intervention), immediately following the end of the intervention period, and 12 weeks after the intervention has ended (see Figure 1). All PD participants will follow their regular medication scheme during the study period. This protocol has been approved by the Ethics Committee of Shanghai University of Sport (102772020RT107). All participants who meet the inclusion criteria will sign informed consent prior to the study.

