**FIGURE 1 F1:**
[figure not shown]
Study pipeline.

A recently published protocol “Long-Term Wu Qin Xi Exercise on Response Inhibition and Cortical Connectivity in Parkinson’s Disease: Design and Implementation of a Randomized Controlled Clinical Trial” is similar to the current protocol (Wang Z. et al., 2021). Our protocol considers the whole brain and will use resting-state fMRI to detect the effects of Wuqinxi on PD patients, while the previously published one only take the primary motor cortex and response inhibition related brain regions (dorsal lateral prefrontal cortex, right inferior frontal gyrus, and presupplementary motor area) into consideration and use dual-site paired-pulse transcranial magnetic stimulation to evaluate the cortical connectivity.

We will first follow the methods in Fiorenzato and Kim’s researches to replicate the effects in their work (Kim et al., 2017; Fiorenzato et al., 2019), and then use DFC analysis as the main method to detect the effects of wuqinxin intervention in patients. In order to replicate the effects in Fiorenzato and Kim’s study, HC will be recruited and compared with whole PD patients before the intervention to support that DFC method could be used in our participants. HC will not be involved in the intervention procedure.

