##### Exclusion criteria

•Tai Chi or other exercise habits.•Other diseases that could interfere with conduct of the study protocol.•History of head injury.•Other significant psychiatric, neurological, or systemic comorbidity.•MRI signal abnormalities (such as cerebral vascular lesions, white matter hyperintensities, and evidence of space-occupying lesions) or artifacts.•Severe cognitive, visual, or auditory impairment.•Depression or anxiety.•MRI contraindications.•Alcohol or drug dependency or abuse.

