### Sample Size Calculation and Blinding

Sample size estimation was performed by G^∗^power V3.1 software (Franz Faul, Universitat Kiel, Germany). According to the analysis, at least 44 participants should be recruited (22 participants per group) in order to be able to perform two-factor repeated ANOVA (within-between interaction) with a middle effect size of 0.25 (Cohen, 1988), level of significance of 0.05, and power of 95% (Mayr et al., 2007). Since some participants may need to be dropped from the analysis due to excessive head motion during scanning, 40 participants will be recruited for each PD subgroup and 40 HC will be recruited. According to a similar studies published recently (Fiorenzato et al., 2019; Chen et al., 2021), this sample size should be adequate for replicating the previous effects in Fiorenzato’s study. In order to attract more participants, we will offer generous compensation and long-term health guidance. Every participant will be offered with an individual exercise plan when the whole study was completed. Randomization of PD patients will be done at the website www.random.org. Two researchers will be trained to assess the outcomes, and they will be blinded to group and will not participate in any interventions.

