### Resting-State and Structural MRI Acquisition and Preprocessing

Resting state functional MRI data and 3D high-dimension T1 image will be collected using a 3T Siemens Magnetom Prisma MRI scanner. PD patients will take medication during MRI scanning to minimize movement artifacts and reduce discomfort. All participants will be instructed to keep their eyes open and focus on a white “+” on black screen, letting their minds wander and trying not to fall asleep during the 10 min 6 s resting state functional MRI scan (gradient echo/fast gradient echo pulse sequence: repetition time = 2000 ms; echo time = 30 ms; flip angle = 80°; matrix size = 106 × 106; number of slices = 62; and voxel size = 2.0 × 2.0 × 2.0 mm^3^ with no gap; number of total volume = 304). During the structural scan participants will be instructed to sleep (repetition time = 3130 ms; echo time = 2.98 ms; flip angle = 4°; matrix size = 256 × 256; number of slice = 176; voxel size = 1.0 × 1.0 × 1.0 mm^3^).

Data preprocessing will be conducted using the SPM12 package implemented in MATLAB R2019a^1^. Prior to preprocessing (1) the first four scans will be deleted from the resting functional volume; (2) functional scans will be realigned to the first volume to correct for interscan head motion; (3) functional scans will be segmented into gray matter, white matter, and cerebrospinal fluid using the Tissue Probability Map template; and finally, and (4) normalized into standard Montreal Neurological Institute space using non-linear transformations and spatially smoothed with a Gaussian smoothing kernel of 6 mm. Participants with head motion greater than 1 mm will be removed from the study (Liao et al., 2014).

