#### Participants’ Characteristics

Demographic characteristics of all participants will be assessed prior to intervention including age, gender, education, age of onset, disease duration, body mass (kg/m^2^), height (cm), and family situation (see Table 1). Levodopa equivalent daily dosages will be calculated for PD patients (Tomlinson et al., 2010).

**TABLE 1 T1:** Demographic characteristics.

	Wuqinxi (*n*)	Balance (*n*)	HC (*n*)	Whole PD vs. HC (*t*/*x*^2^, *p*)	Wuqinxi vs. Balance (*t*/*x*^2^/*F*, *p*)*
Age (year)					
Gender (male%: female%)					
Education (year)					
Age of onset (year)				–	
Hoehn and Yahr stage, *n* (%)					
1–1.5				–	
2–2.5				–	
3				–	
Disease duration				–	
Body mass (Kg/m^2^)					
Height (cm)					
Family situation					
Living along					
Living with husband/wife					
Living with husband/wife and children					
LEDD				–	*****

*The Chi-square test will be used for categorical variables, and two-sample t-test will be run to test between group differences for continuous variables. LEDD = levodopa equivalent daily dose. *Two-factor repeated ANOVA will be applied.*

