##### Group differences in dynamic connectivity: temporal and properties and strength

Group (whole PD patients vs. HC) differences in dwell time, fractional windows, and number of transitions will be examined using two-sample independent *t*-test analysis (*p* < 0.05, FDR correction, see Supplementary Table 1). Covariates will include education, levodopa and dopamine agonist equivalent daily doses. Subsequently, subject-specific medians corresponding to each group-level state will be estimated and two-sample independent *t*-test analysis will be used to compare the connectivity strength of each state at each unique regional pairing (*p* < 0.05, FDR correction) between groups (whole PD patients vs. HC), see Supplementary Table 1. Further, two-sample independent *t*-test analysis will be performed to compare strength abnormalities associated with cognitive deficits by comparing whole PD patients and HC (*p* < 0.05, FDR correction), see Supplementary Table 1.

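### The baseline PD-versus-HC comparison adjusts for dopaminergic dose, which is defined only in the PD patients, so the adjusted difference is an extrapolation to undosed PD

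*Protocol article*

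**What the plan says.** All references are to the Protocol article.

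- **Purpose.** The text under Figure 1 says "HC will be recruited and compared with whole PD patients before the intervention to support that DFC method could be used in our participants". This is the replication step, done at baseline.
- **Comparison.** Under Replication of the previous effects, in the subsection on group differences in dynamic connectivity, "Group (whole PD patients vs. HC) differences in dwell time, fractional windows, and number of transitions will be examined using two-sample independent" t-tests with FDR correction. The next sentence reads "Covariates will include education, levodopa and dopamine agonist equivalent daily doses".
- **Who has a dose.** Participants' Characteristics says "Levodopa equivalent daily dosages will be calculated for PD patients". In Table 1 the levodopa-equivalent row has a dash in the PD-versus-HC column, as do age of onset, Hoehn and Yahr stage and disease duration, which exist only in patients.
- **Medication status.** For patients, "All PD participants will follow their regular medication scheme during the study period", and "PD patients will take medication during MRI scanning to minimize movement artifacts and reduce discomfort". The HC exclusion criteria include "Other significant psychiatric, neurological, or systemic comorbidity", so HC can be expected to take no dopaminergic drugs.
- **Numbers.** "40 participants will be recruited for each PD subgroup and 40 HC will be recruited", which gives 80 PD patients and 40 HC.

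The article does not restrict the dose terms to the PD patients and does not say what value HC receive.

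**The concern.** A covariate can adjust a two-group comparison only where the groups overlap on it. Here one group has a spread of doses and the other has zero or no value. The plan treats dose as not comparable between PD and HC in Table 1, then adjusts for it between PD and HC in the analysis.

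The replication step is the reason the 40 HC are recruited, and it is meant to show that the method works in this sample before it is used on the intervention. If the adjusted contrast is imprecise, or answers a question about patients who were not studied, a failure to replicate could come from the covariate and say nothing about the method.

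**Working it through.** **The plan's own figure.** The only sample-size figure is 44 patients for the randomised two-factor repeated ANOVA. It reproduces (power 0.956) with three time points, a correlation of 0.5 between them and no sphericity correction; those last two settings are assumed defaults. It does not bear on PD versus HC, for which no power or precision figure is stated.

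**Inputs.** From the article: 80 PD, 40 HC, two-sided 0.05. Assumed, because the article gives no dose distribution or effect size: PD mean dose = r × its SD, with r = 1, 1.5 or 2; HC dose = 0; true difference 0.5 SD; power before FDR correction; education ignored.

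**Step 1: what the adjusted effect estimates.** In a linear model on group and dose, the dose slope b comes from within-group variation in dose. HC dose is constant, so b is the PD-only slope. Then

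adjusted effect = (PD mean outcome − b × PD mean dose) − HC mean outcome.

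The bracket is the PD line read at zero dose. In 2,000 simulated data sets (80 versus 40, PD dose mean 1, SD about 0.5), both identities held to rounding error (largest discrepancy below 3 × 10⁻¹⁵). The result holds for any dose spread. Only patients with zero dose would give the line any data at that point.

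If HC dose is left missing, a complete-case fit has no HC and the comparison cannot be made.

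**Step 2: loss of precision.** With HC share q = 40/120 = 1/3, the squared correlation between group and dose is R² = q r² / (1 + q r²). The variance inflation factor is VIF = 1/(1 − R²) = 1 + r²/3.

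The unadjusted standard error is √(1/80 + 1/40) = 0.194 SD, so the noncentrality is 0.5 / (0.194 × √VIF).

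| PD mean / SD of dose | R² | VIF | SE multiplied by | Power |
|---|---|---|---|---|
| no dose covariate | – | 1 | 1 | 0.73 |
| 1 | 0.25 | 1.33 | 1.15 | 0.60 |
| 1.5 | 0.43 | 1.75 | 1.32 | 0.49 |
| 2 | 0.57 | 2.33 | 1.53 | 0.39 |

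The simulation, at a ratio of about 2, gave power of 0.73 unadjusted and 0.37 adjusted, in line with the last row.

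The plan names levodopa and agonist dose, which may be two covariates. If they are independent within PD with mean/SD of 2 and 1, VIF = 1 + (4 + 1)/3 = 2.67, the SE is multiplied by 1.63 and power is 0.35.

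**Step 3: shift of the estimate.** Adjustment moves the group effect by b × PD mean dose. In SDs of the outcome within PD this is ρ × r, where ρ is the within-PD correlation of dose with outcome. For illustration, ρ = 0.2 gives 0.2 SD at r = 1 and 0.4 SD at r = 2, against an assumed effect of 0.5 SD. The direction depends on the sign of ρ, which the article does not give.

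**The case against.** **Scope.** The strongest reply is that this is a baseline check. HC take no part in the intervention, both randomised arms have doses, and no rule makes the trial analysis depend on successful replication. All of this stands and limits the point to the replication step. The covariate sentence also follows the temporal-measure comparison; the two connectivity-strength comparisons after it list no covariates.

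**Terminology.** A two-sample t-test has no covariates, but a two-group linear model is often called one, so the label is loose and not a second defect. Coding of HC may be settled in a fuller plan. That would decide between Step 1's two outcomes, but neither gives a usable adjusted PD-versus-HC effect.

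**Stronger readings that a reader might infer, and that the article does not support:**

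- *Dose is nearly a duplicate of group.* That depends on the dose spread. R² runs from 0.25 to 0.57 in the table, below one half in two of the three cases. The extrapolation does not depend on this.
- *The adjustment could reverse the sign of the PD effect.* Cancelling 0.5 SD needs a within-PD correlation of 0.5 (r = 1) down to 0.25 (r = 2), in the right direction. The article gives no such value and does not say that dose follows disease severity.
- *The arm comparison adjusts for post-randomisation dose.* The same covariate sentence appears there, but without saying which visit's dose is used. The Table 1 footnote makes dose a variable to be compared across visits; it does not put follow-up doses into the connectivity model.

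**Conclusion.** The point holds for the baseline PD-versus-HC comparison of the three temporal measures. The dose adjustment is stated in the text, and it either extrapolates to undosed PD (HC at zero) or removes the HC (HC missing). The extrapolation follows from the article alone, provided that HC take no dopaminergic drugs and that essentially all PD patients do.

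The size rests on assumptions. For a PD mean dose of 1 to 2 SD and a 0.5 SD difference, the standard error rises by 15% to 53% and uncorrected power falls from 73% to between 60% and 39%. More homogeneous doses would make it worse. Any within-PD association between dose and outcome adds a shift of unknown sign.

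The limitations in the Discussion admit a possible effect of dopaminergic therapy on connectivity, but not that this adjustment cannot separate drug from disease when every treated participant is a patient. The randomised comparison does not share the defect.

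**What to change.** In the baseline PD-versus-HC analysis of the temporal measures:

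1. Remove levodopa and agonist dose from the main model.
2. Name the method as a linear model (ANCOVA) of each measure on group with education, keeping the planned FDR correction.
3. Examine the relation of dose to the temporal measures within the 80 PD patients only. If a dose-adjusted PD-versus-HC result is still wanted, report it as a sensitivity analysis, state that HC are coded as zero, and describe the estimate as extrapolated to zero dose.
4. Describe the main result as medicated PD versus HC.

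This changes wording only and needs no new data or participants. The price is that the main contrast combines disease and treatment, which the planned adjustment cannot separate either.

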### Participants

#### Parkinson’s Disease Patients

##### Inclusion criteria

•Patients with PD diagnosed according to the UK Parkinson’s Disease Society Brain Bank diagnostic criteria.•Age 55–75 years old.•Hoehn and Yahr (H&Y) score of 1–3.•20≤ Montreal Cognitive Assessment (MoCA) score ≤25.•Ability to walk and exercise independently.

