#### Healthy Controls

##### Inclusion criteria

•Age 55–75 years old.•Ability to walk and exercise independently.

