#### Primary Outcome Assessment

The Montreal Cognitive Assessment (Nasreddine et al., 2005) will be conducted to assess cognitive impairment and the Repeatable Battery for the Assessment of Neuropsychological Status (Stella et al., 2013) will be used to measure the cognitive domains of immediate memory, visuospatial, language, attention, and delayed memory (see Supplementary Table 1). Dynamic states, dwell times, fractional windows, and number of transitions will be computed to reflect the characteristics of DFC (see Supplementary Table 1).

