#### Replication of the previous effects

##### Clinical and Neuropsychological Data Analysis

Statistical analyses will be performed using SPSS version 19.0. Demographic and clinical information of all PD patients will be compared using two-sample independent *t*-test (see Table 1). Pearson’s chi-square test will be used to compare categorical variables (see Table 1). Pearson’s correlation analyses will be applied between temporal properties and cognition (MoCA and cognitive performance in each domain) in whole PD patients as well as motor severity (UPDRS-III) before the intervention (see Table 2). The threshold for statistical significance will be set at *p* < 0.05.

**TABLE 2 T2:** Correlation between dynamic functional connectivity temporal properties and clinical characteristics (before intervention, after intervention, and follow-up).

		UPDRS-III	MoCA	Cognitive domains				
				I-M	V	L	A	D-M
Dwell time state I	*r*							
	*p*-Value							
Dwell time state II	*r*							
	*p*-Value							
Fractional windows	*r*							
	*p*-Value							
Number of transitions	*r*							
	*p*-Value							

*I-M = immediate memory; V = visuospatial; L = language; A = attention; D-M = delayed memory.*

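### The baseline strength test labelled as cognition-related is a whole-PD-versus-HC t-test with no cognitive variable, so it cannot separate cognition from Parkinson's disease or its medication

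*Protocol article*

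**What the plan says.** The Protocol article, under Replication of the previous effects (subsection on group differences in dynamic connectivity), plans two successive tests of connectivity strength at baseline. In the first, "two-sample independent *t*-test analysis will be used to compare the connectivity strength of each state at each unique regional pairing", with all PD patients set against HC and an FDR-corrected threshold of 0.05. The second will "compare strength abnormalities associated with cognitive deficits by comparing whole PD patients and HC", again by two-sample t-test at an FDR-corrected 0.05. Both refer to Supplementary Table 1.

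On who enters the contrast:

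- The PD inclusion criteria require "20≤ Montreal Cognitive Assessment (MoCA) score ≤25". Primary Outcome Assessment says that the MoCA "will be conducted to assess cognitive impairment".
- The HC inclusion list consists of an age range and "Ability to walk and exercise independently". The only cognitive rule for controls is the exclusion of "Severe cognitive, visual, or auditory impairment".

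On where cognition does enter: under Clinical and Neuropsychological Data Analysis, "Pearson’s correlation analyses will be applied between temporal properties and cognition (MoCA and cognitive performance in each domain) in whole PD patients". Table 2 lists the imaging variables for these correlations: dwell time in each state, fractional windows and number of transitions.

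Under Application of DFC in Wuqinxi Intervention, the cognitive-deficit label returns for a two-factor repeated ANOVA of the Wuqinxi and balance groups over time.

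**The concern.** The label promises a finding about cognition, but the contrast under it is one of diagnosis. If the plan is followed as written, regional pairings that differ between PD and HC will be reported as abnormalities tied to cognitive deficits, although nothing in the test distinguishes cognition from the disease or its treatment. Medication is a live alternative: patients are scanned on medication, and the Discussion concedes that dopaminergic therapy may affect functional connectivity.

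This matters because Design and Procedures gives the PD-HC comparison the task of supporting the use of DFC in these participants, and the trial's stated aim concerns cognitive impairment. A mislabelled result here would lend the strength measures a cognitive meaning that they have not earned.

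**Working it through.** The plan gives no figure for this test. Its sample size of 44 concerns the repeated-measures interaction and plays no part here.

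**1. The two strength tests side by side**

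| | First strength test | Cognitive-deficit test |
|---|---|---|
| Method | two-sample t-test | two-sample t-test |
| Groups | whole PD, HC | whole PD, HC |
| Outcome | strength by state and pairing | strength; pairings not specified |
| Threshold | 0.05, FDR | 0.05, FDR |
| Cognitive variable | none | none |

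The covariates in that subsection are listed with the temporal-property comparison: education and the two dopaminergic dose measures. The covariates regressed out earlier, under Sliding Window Approach, are age, gender and education. Neither list contains a cognitive score.

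**2. What the contrast estimates**

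Inputs: 80 PD (40 + 40) and 40 HC, from Sample Size Calculation and Blinding; MoCA 20-25 for all PD. Assumption: impairment is coded as MoCA of 25 or below (the protocol states no cut-off). All 80 patients are then impaired, and h of the 40 controls may be. Write strength as

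Y = a + b·PD + c·IMP + error,

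where b carries everything that goes with PD, medication included, and c carries cognition. The expected PD-HC difference is

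D = b + c·(1 − h/40).

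For h = 0, 4, 8 and 12 (an assumed range) this is b + c, b + 0.90c, b + 0.80c and b + 0.70c. There is one number for two unknowns. In every case D fits b = D with c = 0, and equally b = 0 with c = D/(1 − h/40).

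**3. Would adding an impairment indicator to the PD-HC model help?**

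The squared correlation between the PD and IMP indicators is r² = 80(40 − h) / [40(80 + h)] = 2(40 − h)/(80 + h), and VIF = 1/(1 − r²).

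| Impaired HC (h) | r² | r | VIF |
|---|---|---|---|
| 0 | 80/80 = 1 | 1.00 | infinite (design rank 2 of 3) |
| 4 | 72/84 = 0.857 | 0.93 | 7.0 |
| 8 | 64/88 = 0.727 | 0.85 | 3.7 |
| 12 | 56/92 = 0.609 | 0.78 | 2.6 |

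With no impaired control, separation is impossible. With some, it is weakly possible, but only in a model that contains cognition. The planned t-test does not.

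**4. Does another planned analysis fill the gap?**

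The correlations within PD, in both the replication and the intervention stage, use the Table 2 variables. Connectivity strength is not among them, so no stated analysis relates strength to cognition among patients.

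**The case against.** Four points can be made for the plan.

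*The second test may not repeat the first.* A reader might infer that the two strength tests are identical and must return the same result. The documents do not establish this. The second does not repeat the specification of every regional pairing, and Supplementary Table 1 may restrict it to a chosen set, which would change the FDR family. This stands against calling it an exact duplicate. It does not rescue the label, because any subset of a PD-HC contrast is still a PD-HC contrast.

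*Impairment of all patients is a reading.* The protocol gives a MoCA range and no threshold. The point does not need one: no PD patient outside 20-25 is available, and no cognitive term is in the test.

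*The consequence is contained.* HC are compared only before the intervention, and no comparison of Wuqinxi with balance depends on them. The temporal properties, which Primary Outcome Assessment names as the DFC outcomes, do get correlations with cognition within PD. This stands, and it limits the damage to what is claimed about strength.

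*The aliasing does not extend to the arms.* A reader might carry it over to the intervention stage. That would be wrong: both arms are randomised PD patients, so diagnosis cannot be confused with arm. Only the unsupported label carries over.

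**Conclusion.** The concern holds for the label and for what the contrast can identify. The baseline test presented as concerning cognitive deficits estimates the difference between PD patients with MoCA 20-25 and HC. The part of that difference due to cognition is not identifiable from it, whatever its size. This rests on the stated contrast, the stated entry range and the absence of any cognitive variable; the impairment coding and the numbers of impaired controls above are illustrations only.

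Two stronger inferences are not supported. A reader might try to size the problem through loss of power from the narrow MoCA range. That needs a true correlation and an unrestricted SD which the protocol does not give, and it concerns a correlation, not this t-test. A reader might also conclude that controls need a MoCA entry rule. Controls with low scores are possible but not shown, and such a rule would change eligibility without putting a cognitive term into the test.

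The randomised comparison of cognitive outcomes is unaffected. The defect should be corrected before the strength results are analysed and interpreted.

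**What to change.** 1. Label the PD-HC strength result as *PD with MoCA 20-25 versus HC*.
2. Replace the cognitive-deficit test with a baseline analysis within PD (n up to 80, fewer after head-motion exclusions). Relate connectivity strength in each state to the RBANS domain scores, adjusted for UPDRS-III, levodopa-equivalent dose and education, with FDR correction.
3. Preferably limit that analysis to pairings that differ between PD and HC, stated in advance. Without a limit, up to 100 components give 100 × 99/2 = 4,950 pairings; two states and five domains make up to 4,950 × 2 × 5 = 49,500 tests. The price is that a pairing related to cognition but not differing between PD and HC would be missed.
4. In the intervention stage, relate change in strength to change in RBANS, or drop the label.
5. Report baseline MoCA in HC if it is collected. No new entry criterion is needed.

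The cost is revised wording and some extra analysis of data already planned for PD patients, with no change to eligibility, randomisation or patient assessments. The downside is a more modest claim from the PD-HC contrast.
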